## Abstract

**Background:**

The primary objective of this trial is to examine the mechanisms of time-restricted eating (TRE) as an adjunct to psychiatric care for people with bipolar disorder (BD) with sleep or circadian disruptions. This study builds on prior studies of circadian disruption in BD as well as growing evidence that TRE improves circadian functioning.

**Methods:**

One-hundred fifty participants diagnosed with BD 1 or II will be recruited via advertising in the local community. Main inclusion criteria include: obtaining medical treatment for BD; current sleep or circadian problems; self-reported eating period of ≥ 12 h; no eating disorder or other health conditions that would hinder or limit the safety of following TRE; and not currently experiencing a mood episode, acute suicidality, psychosis, alcohol or substance use disorder. Participants will be asked to complete a baseline period in which daily food intake is logged online for two weeks. After baseline, participants will be asked to follow TRE for 8 weeks and to continue to complete daily food logging during this time. Symptom severity interviews will be conducted by phone or videoconference at baseline, mid-intervention (6 weeks post-baseline), end of intervention (10 weeks post-baseline), and 6 months post-baseline. Self-rated symptom severity and quality of life data will be gathered online at the same time points as symptom severity interviews, and at 16 weeks post-baseline (6 weeks after the TRE period ends). To assess potential mechanisms of change, we will examine the change in diurnal amplitude of ‘clock’ gene expression as a primary mediator at 8 weeks compared to baseline. We will further test whether diurnal amplitude of clock gene expression is predictive above and beyond the role of two covariate potential mediators, glucose tolerance and inflammation at 8 weeks relative to baseline. To provide an index of whether TRE successfully decreases emotional lability, participants will be asked to complete 5 mood assessments per day for 7 days at baseline and at 10 weeks. These mood assessments will be optional.

**Discussion:**

The planned research will provide novel and important information on whether TRE improves sleep/circadian rhythm problems, along with reductions in mood symptoms and improvements in quality of life, for individuals with BD.

**Trial registration:**

ClinicalTrials.gov ID: NCT06555406.

## Background

Bipolar disorder (BD) is a severe, recurrent mood disorder defined primarily by manic symptoms. Different forms of BD have been defined based on the severity and duration of manic symptoms. BD is the fifth leading mental health contributor to global disability [1], and it is all too often tied to unemployment, legal problems, and severe functional impairment [1–5].

Disruptions to sleep/wake cycles and diurnal rhythms in activity and biological functioning are frequently observed in patients with BD and may give rise to, or exacerbate, symptoms. Building on findings over the last decade showing that time-restricted eating (TRE), where eating is limited to 6–10 h during the day, improves diurnal rhythms in metabolic factors and in hormones and the genes underlying circadian function [6–11], the present study seeks to determine if (1) TRE reduces mood symptoms and improves quality of life, and (2) if changes in mood symptoms are related to improved diurnal rhythms in behavior and physiology among those with BD who experience sleep or circadian issues.

### Time-restricted eating (TRE)

The circadian timing system consists of a hierarchy of oscillators controlled by a central pacemaker in the suprachiasmatic nucleus (SCN). The SCN is entrained to the environment via a direct pathway from the retina [12]. Coherence among oscillatory cells in central and peripheral systems is maintained by multi-synaptic, autonomic innervation of peripheral systems by the SCN and central clock control of hormones that target the periphery [13, 14]. Disturbances to this coordinated rhythmic harmony are linked to significant mental and physical health risks [13].

In addition to autonomic innervation and hormonal communication, the timing of food intake can also set the phase of peripheral tissues, without impact on the SCN [15], leading to incongruence between central pacemaker and peripheral systems. Under circumstances where food is ingested during the active phase of the day, systemwide synchrony occurs. However, when eating occurs outside of the active phase, the light-entrained SCN and periphery are at odds in their timing. Seminal work in mouse models established that restricting feeding to the active portion of the day (i.e., the dark phase of the day) improves rhythms in the genes regulating circadian function, improves metabolic functioning (e.g., glucose tolerance and insulin resistance) [7–9, 16–19], and increases longevity independent of changes in caloric intake [20]. Thus, by coordinating peripheral oscillators and the SCN during the day, time-restricted feeding (TRF) helps coordinate circadian rhythms between brain cells in the SCN and cells within other organs (e.g., the liver, lungs, and kidneys) [21, 22]. Indeed, converging evidence across studies indicates that at least some metabolic benefits of TRF result from the resetting the phase of peripheral circadian rhythms [21].

Based on these foundational findings in animal models, the benefits of time-restricted eating (TRE) have received significant attention for human health studies. Across at least 14 randomized controlled trials, substantial metabolic benefits have been observed in glucose regulation and, in many studies, decreased body mass index, including several studies with large sample sizes [23]. In a randomized controlled trial of 80 healthy males, TRE upregulation of the ‘clock’ genes *BMAL1, CLOCK*, and *SIRT1* was observed in serum, suggesting that TRE enhances rhythmic amplitude [24]. As observed under TRF in mice, TRE was shown to shift circadian rhythm of clock gene expression in two smaller studies [10, 11].

High satisfaction and adherence are reported by participants assigned to TRE [21, 25] that likely stem from its health benefits and improvements to sleep duration, sleep efficiency, and reductions in sleep timing variability [25, 26]. Participants report improved energy and restedness within a few weeks of beginning TRE that are sustained for at least six months post-intervention [11, 25]. In fact, several studies report that TRE enhances perceived subjective sleep quality and restedness [11, 25, 27]. Across studies, participants assigned to TRE report significantly improved quality of life ratings from baseline to the 6-month follow-up [27–30]. Of note, TRE does not seem to increase hunger [21, 31], reduce muscle mass [32], or negatively impact cognitive function [33].

### Circadian and sleep disruption in bipolar disorder (BD)

Considerable evidence supports a strong association between biological rhythm disturbances and the pathogenesis of BD [34]. Disturbed sleep-activity rhythms are principal symptoms observed in manic and depressive episodes [35, 36], and these disturbances continue at lower levels for most people with BD during remission [37–40]. Sleep disturbances predict both BD onset and symptom increases in naturalistic studies of sleep, jet lag, activity, and sleep deprivation [40–45]. These issues predict vulnerability to the disorder, with evidence linking (a) BD to single-nucleotide polymorphisms within multiple clock genes, (b) mood variability to polygenic risk scores related to chronotype and low circadian amplitude, and (c) disruptions in sleep/sleep-activity rhythms [46–48] in family members of those diagnosed with BD. Accordingly, there is a need for interventions that target the circadian timing system to stabilize biological rhythms in patients with BD.

#### Biological rhythm intervention in BD

Both in people with BD and in animal models of BD, psychopharmacological and psychotherapeutic treatments impact circadian function, suggesting that improvements to circadian rhythmicity impact treatment outcome. Considerable evidence from animal studies reveals that lithium and antidepressants influence circadian rhythms through actions affecting SCN neuronal firing and clock gene expression [49–53]. In people with BD, differences in neuronal circadian rhythms from patient-derived pluripotent stem cells predict lithium response [54], and psychosocial therapy for mood disorders decreases REM density while improving symptoms [55–57]. Preliminary research shows benefits of pharmacological agents, such as the selective melatonin receptor type I and II agonists ramelteon and agomelatine, as mood stabilizers, suggesting potential therapeutic actions via alterations in circadian rhythms in sleep [58, 59].

Behavioral treatments for BD focus on improving sleep and circadian function, and include interventions such as restricting activity during dark periods [60, 61], interpersonal and social rhythm therapy (IPSRT) [62], and light therapy [63]. However, there are limitations in available treatments designed to address sleep and circadian rhythms in BD and further treatment developments that produce reliable outcomes across individuals and long-term are needed [64].

#### The applicability of the TRE to mood disorders

Although no studies have examined TRE as a BD-specific intervention, some trials considered mood changes among participants without diagnosable mood disorders following TRE. In the only published RCT, TRE decreased depression scores in those with type 2 diabetes compared to a control condition [65]. Likewise, TRE improved quality of life compared to a control condition in a study of shift workers [66]. Significant decreases in pre- to post-depression scores were not observed in uncontrolled studies of TRE [67, 68], potentially due to low depressive symptom levels at baseline.

To examine the potential efficacy of TRE in BD, we completed the first study examining the effects of TRE among patients with BD [69]. 207 participants who self-identified as having BD were surveyed and reported attempting TRE (daily food intake window of < 14 h) for at least several weeks. For all outcomes assessed, 51–66% of participants reported improvements (“better” or “much better”) while applying TRE, and 99% of participants reported gains in at least one domain. These preliminary findings are especially promising given that participants were implementing TRE without the formal support that will be provided in this trial.

### Project aims

The aim of this study is to examine the mechanisms through which TRE influences symptom improvement in BD. We will assign all participants to TRE and will measure diurnal amplitudes and phases of clock gene expression (mRNA) responsible for circadian rhythm generation at the cellular level, as well as dim light melatonin onset (DLMO), the standard measure of circadian phase. We will examine whether changes in the diurnal amplitude predict improved symptoms and quality of life (QoL)—an ideal test of the circadian rhythm hypothesis of BD. To maximize the ability to show that TRE leads to changes in diurnal rhythms, we will recruit individuals who are (a) diagnosed with BD, (b) have at least some symptoms of circadian rhythm sleep–wake disorders or sleep disorders, and (c) report an eating window of ≥ 12 h.

Although our data will be preliminary, we also aim to gather information about two other potential biological mechanisms of TRE: changes in pro-inflammatory cytokines and glucose tolerance. Across studies, TRE rapidly attenuates night-time, fasting, and 24-h glucose levels, with effects sustained across 3–5 weeks of TRE as well as improved glucose tolerance, improved insulin sensitivity and resistance, and lower HbA1c within 3–6 weeks [23]. This is of importance given that over 22% of those with BD show insulin resistance and another 33% have type II diabetes; insulin resistance among those with BD predicts robustly worse symptom course, rapid cycling, treatment resistance to lithium [70], and worse neurocognitive performance. Recent pilot work showed that symptoms of BD were reduced substantially among 50% of patients who were treated with metformin, a diabetes medication [71].

TRE has been found to be associated with significant pre-post reduced pro-inflammatory cytokines, and decreased biomarkers indicative of oxidative stress [72, 73]. Therefore, substantial evidence links inflammation to BD. We will assess and control for changes in pro-inflammatory cytokines and glucose tolerance in examining circadian rhythm normalization as a mediator. This will supply critical mechanistic information to explain individual differences in responsivity to TRE.

Our goal is to examine TRE as an adjunct to psychiatric care for BD. Accordingly, participants will be asked to sustain ongoing medical care for BD.

#### Hypotheses

To examine the mechanisms through which TRE leads to symptom improvements, we will investigate a battery of biological measures at baseline and 8 weeks. We predict that TRE adherence will lead to a change in the amplitudes of diurnal clock gene expression and diurnal phase (DLMO) at 8 weeks, which will lead to a cascade of change in symptoms (mania and depression at week 10, and then a downstream change in QOL at 16 weeks).

H1: TRE adherence will predict changes in diurnal amplitude of clock gene expression from baseline to week 8.H2: The degree of change in diurnal amplitude of clock gene expression (at week 8) will be associated with the degree of improvement in symptoms (week 10), controlling for change in glucose tolerance and inflammation (week 8) and for baseline levels of diurnal amplitude, symptoms, glucose tolerance, and inflammation.H3: There will be an indirect effect of TRE adherence on QoL through symptoms.

Ambulatory data will provide opportunity for lagged tests of how biological rhythmicity improvements (actigraphy RA) promote improved sleep, resulting in diminished mood variability (ecological momentary assessment; EMA Mood Zoom) [74].

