### Trial design

The trial is a non-randomized, single arm (TRE) study. The primary endpoint is immediately after the 8-week-long TRE period (end of week 10). The follow-up assessments will be conducted at 6 months after the baseline, supplemented with post-baseline self-reported assessment at week 16. Hypothesized mechanisms of change will be tested at baseline and at 8 weeks post-baseline. The study setting is remote (online food plan materials, questionnaires, and interviews), supplemented with at-home collection of biological data (DLMO, clock genes, actigraphy, CGM) and assays completed by Quest Diagnostics (CMP, glucose tolerance test).

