***Primary Outcome Measures***							
Montgomery-Asberg Depression Rating Scale (MADRS)	I		X	X	X		X
Young Mania Rating Scale (YMRS)	I		X	X	X		X
Brief Quality of Life in Bipolar Disorder (QoL.BD)	SR		X	X	X	X	X

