### Statistical analysis plan

Before conducting analyses of hypotheses, we will examine whether values appear to be missing at random. If this missing value imputation assumption is supported, we will impute data using 20 resamples, using demographic (sex/gender, age), baseline symptom severity, and symptom history variables (number of episodes) to predict missing scores. For comparison, we will perform analyses without imputed values. Data cleaning will be completed as described above in data quality. Statistical analyses will be conducted in accordance with the International Conference on Harmonization E9 statistical principles.

Before conducting analyses of hypotheses, we will carefully examine potential confounds. We will avoid adding any covariates that were entangled with our core mechanisms (e.g., sleep and circadian processes). With this in mind, we will only consider covariates for inclusion in models if they could be confounding our main effects– that is, those that are significantly correlated with both our IV (treatment adherence) and DVs (symptoms and QoL). Power analyses were based on inclusion of two covariates, and we would hope not to exceed this number of covariates. If more than two potential covariates are identified that appear significantly and uniquely correlated with both the IV and DVs, we would redo our power analyses, but at this point, we would be able to consider the covariance matrices, allowing for more careful estimation of true statistical power. We would consider these issues without generating the models of how our treatment variables actually influence symptoms and QoL, so as to avoid p-hacking or “fishing”. Only if those power analyses suggested that we could include more than 2 variables as confounds would we proceed to add more covariates; otherwise, we would plan to choose the two covariates that appear to hold the highest unique correlations with IV and DVs.

Analyses will be conducted using two-tailed tests with alpha set to .05.

Our core hypotheses will be tested using two parallel structural equation models (SEM) to consider mania and depression separately. In each, we will examine paths from TRE adherence levels to a latent variable for clock gene amplitude (based on 3 genes) to symptoms to QoL, controlling expected covariates and evaluating the potential confound of glucose tolerance mediation.

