We have planned analyses based on availability of data from 125 participants, allowing for attrition of 25 participants. We assume moderate effects for diurnal amplitude on symptoms and QoL (f2 = .25) because smaller effects are inconsistent with the circadian rhythm theory. Assuming f2 = .40 (symptoms to QoL), power to detect the indirect effect of change in amplitude of gene expression on QoL via symptom change is .81, and for full model (RMSEA) > .90 [130, 131]. Intervention-related effects will be estimated using an intention-to-treat approach, in which we will examine final scores (where available) for all participants.

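### Baseline QoL.BD is collected but named in no control list, so the symptom-to-QoL path behind H3 can be confounded by prior quality of life

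*Protocol article*

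**What the plan says.** All references are to the protocol article.

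- **Design.** Under Trial design: "The trial is a non-randomized, single arm (TRE) study". Adherence, clock gene amplitude, symptoms and QoL are therefore all observed, and none is assigned.
- **Baseline QoL.** Table 1 lists QoL.BD among the primary outcome measures and marks it at baseline and at every later assessment.
- **Controls in the hypotheses.** H2 controls for change in glucose tolerance and inflammation and "for baseline levels of diurnal amplitude, symptoms, glucose tolerance, and inflammation". H5 and H6, whose outcome is symptoms, also control for baseline symptoms. H3 reads "There will be an indirect effect of TRE adherence on QoL through symptoms" and names no control.
- **Core model.** The Statistical analysis plan section describes two parallel SEMs, one for mania and one for depression. Each runs from adherence to amplitude to symptoms to QoL. They adjust for covariates that the section calls expected but does not list.
- **Covariate rule.** The same section considers covariates only if they are "those that are significantly correlated with both our IV (treatment adherence) and DVs (symptoms and QoL"), with two as the planned maximum unless power is recalculated.
- **Form of the QoL outcome.** The text introducing the hypotheses speaks of QoL changing by week 16. The intention-to-treat sentence says "we will examine final scores (where available) for all participants".

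**The concern.** The symptom-to-QoL path is the last link of the H3 chain. Its exposure is week-10 symptoms and its outcome is later QoL. A person whose QoL was already good at baseline may have fewer symptoms at week 10 and will probably report better QoL afterwards. Randomisation does not break that link here. If baseline QoL is left out, part of a stable difference between people can be read as symptom relief producing better QoL.

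The covariate rule does not reliably protect against this. It asks whether a candidate correlates with adherence, but a confounder of the symptom-to-QoL path need not do so. However strongly baseline QoL predicts later QoL, it could fail that test.

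**Working it through.** **Inputs from the article.** N = 125 analysed ("availability of data from 125 participants, allowing for attrition of 25 participants") and two-sided testing at .05 ("Analyses will be conducted using two-tailed tests with alpha set to .05"). The article gives no correlation of baseline QoL with symptoms, later QoL or adherence, so those values are assumptions shown as ranges.

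**The plan's own figure.** The article states power of .81 for the indirect effect of amplitude change on QoL. With f2 = .25 and .40 as written and N = 125, the two path powers are .9998 and 1.000, jointly .9998, so .81 is not reproduced. That is a separate matter, and nothing below rests on it.

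**Step 1: the adherence screen.** At N = 125 a correlation needs to reach about .176 to be significant. By Fisher's z, the chance that baseline QoL passes is:

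| True correlation with adherence | 0 | .05 | .10 | .15 | .20 | .25 |
|---|---|---|---|---|---|---|
| Chance of passing | .05 | .09 | .20 | .39 | .61 | .81 |

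Up to a true correlation of .15 it is more often kept out than let in.

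**Step 2: bias when baseline QoL is omitted.** Variables are standardised: Q0 and S0 are baseline QoL and symptoms, S1 is week-10 symptoms, Q1 is later QoL. Assumptions: r = corr(Q0, S0) = -.5; path s from S0 to S1 = .4; direct path g from Q0 to S1 = 0 to -.35; QoL stability ρ (path from Q0 to Q1) = .5 or .7; true S1-to-Q1 path = 0. The fitted equation is Q1 on S1 and S0.

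- Variance of S1 given S0: V = 1 - (s + g·r)²
- Spurious path: b = ρ·g·(1 - r²)/V
- Residual variance: R = (1 - ρ²) + ρ²·[(1 - r²) - g²(1 - r²)²/V]
- Standard error: SE = √(R/[(N - 3)·V])
- Rejection rate ≈ Φ(|b|/SE - 1.96) + Φ(-|b|/SE - 1.96)

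For g = -.25 and ρ = .5:

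- V = 1 - .525² = .724
- b = .5 × (-.1875)/.724 = -.129
- R = .75 + .25 × (.75 - .0485) = .925
- SE = √(.925/(122 × .724)) = .102
- |b|/SE = 1.265, so the rejection rate is about 24%

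| Direct path g | Spurious b, ρ = .5 | False positive, ρ = .5 | Spurious b, ρ = .7 | False positive, ρ = .7 |
|---|---|---|---|---|
| 0 | 0 | 5% | 0 | 5% |
| -.15 | -.073 | 11% | -.102 | 19% |
| -.25 | -.129 | 24% | -.181 | 45% |
| -.35 | -.196 | 46% | -.275 | 78% |

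Simulation agrees to within about two percentage points (76% in the last cell). At ρ = .3 the rates for the three non-zero paths are about 7%, 11% and 19%. With baseline QoL in the equation the bias is zero and the rate is about 5% in every cell.

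**Step 3: if QoL is modelled as a raw change score.** The spurious path becomes (ρ - 1)·g·(1 - r²)/V. At g = -.25 this is +.129 for ρ = .5 and +.078 for ρ = .7. The sign is opposite to the one H3 predicts. The bias is reversed, not removed.

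**Step 4: precision.** At g = -.25, the SE with baseline QoL divided by the SE without it is about 1.00, .94 and .80 at ρ = .3, .5 and .7. Collinearity with week-10 symptoms offsets part of the gain in residual variance.

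**The case against.** - **The screen may not apply to baseline levels.** H2 already fixes four baseline controls without screening, which is more than the two that the rule allows. Baseline QoL could likewise be among the unlisted expected covariates. This is a fair reading, so a reader should not infer that the plan definitely excludes baseline QoL. What stands is that no list includes it, and the one stated route for further covariates uses the wrong test.
- **H3 is one line, and an article condenses.** H1 names no controls either, and the three hypotheses are paths in one SEM. That weakens any inference from H3's silence alone. But the article does give control lists and does fix a covariate rule, so the point concerns what is stated and not a detail left to a fuller plan.
- **The final-scores sentence concerns intention-to-treat.** A reader might take it as proof that QoL enters as an unadjusted endpoint. The documents do not support that: the sentence is about who is analysed. If change is meant instead, the false support for H3 disappears, but Step 3 shows bias the other way.
- **The bias can be zero.** This is so when baseline symptoms are in the QoL equation and baseline QoL has no direct effect on week-10 symptoms. The first condition is not stated for the QoL equation.
- **One path is not H3.** A reader might take 11% to 78% as the false-positive rate for H3. It is not: the indirect effect also needs the upstream paths, so under a joint-significance test its rate cannot exceed that of this path.
- **Power.** A reader might expect a clear power gain from adjustment. Step 4 does not support claiming one.

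**Conclusion.** The point holds in this form: baseline QoL.BD is available, no stated control list contains it, and the rule for adding covariates screens on adherence although the exposure on this path is symptoms. The symptom-to-QoL link in H3 is therefore open to confounding by prior QoL. The size rests wholly on the assumed correlations: from no inflation (5% false positives) with no direct path from baseline QoL to week-10 symptoms, to about 11% to 78% for direct paths of -.15 to -.35 with QoL stability of .5 to .7, against 5% after adjustment. The case for change is protection from bias; any gain in precision is secondary and not guaranteed. The change should be made, and fixed before the models are run.

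**What to change.** In both SEMs, enter baseline QoL.BD, together with baseline symptoms, as a fixed covariate of the follow-up QoL equation, exempt from the correlation screen and from the limit of two. Add to H3 the words *controlling for baseline QoL and baseline symptoms*, in line with H2, H5 and H6.

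The data are already in the schedule. The cost is one or two degrees of freedom in the QoL equation, and the estimated symptom-to-QoL path may come out smaller. Settling this in advance also avoids a choice made after seeing the models, which the covariate section sets out to prevent.
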